## Abstract

**Background:**

Chronic obstructive pulmonary disease (COPD) and chronic heart failure (CHF) frequently coexist, significantly reducing patients’ quality of life and increasing morbidity and mortality. For either single disease, a multidisciplinary disease-management approach supported by telecommunication technologies offers the best outcome in terms of prolonged survival and reduced hospital readmissions. However, no data exist in patients with combined COPD/CHF.

We planned a randomized controlled trial to investigate the feasibility and efficacy of an integrated, home-based, medical/nursing intervention plus a rehabilitation program versus conventional care in patients with coexisting COPD/CHF. The purpose of the paper is to describe the rationale and design of the trial.

**Methods/designs:**

Patients, after inpatient rehabilitation, were randomly assigned to the intervention or control group, followed for 4 months at home, then assessed at 4 and 6 months. The intervention group followed a telesurveillance (telephone contacts by nurse and remote monitoring of cardiorespiratory parameters) and home-based rehabilitation program (at least three sessions/week of mini-ergometer exercises, callisthenic exercises and twice weekly pedometer-driven walking, plus telephone contacts by a physiotherapist). Telephone follow-up served to verify compliance to therapy, maintain exercise motivation, educate for early recognition of signs/symptoms, and verify the skills acquired. At baseline and 4 and 6 months, the 6-min Walk Test, dyspnea and fatigue at rest, oxygenation (PaO_2_/FiO_2_), physical activity profile (PASE questionnaire), and QoL (Minnesota and CAT questionnaires) were assessed. During the study, serious clinical events (hospitalizations or deaths) were recorded.

**Discussion:**

Currently, no studies have assessed the impact of a telehealth program in patients with combined COPD and CHF. Our study will show whether this approach is effective in the management of such complex, frail patients who are at very high risk of exacerbations.

**Trial registration:**

Network per la prevenzione e la sanità pubblica, CCM, Ministero della Salute “Modelli innovativi di gestione integrata telegestita ospedale-territorio del malato cronico a fenotipo complesso: studio di implementazione, validazione e impatto,” registered on 14 January 2014.

ClinicalTrials.gov Identifier: NCT02269618, registered on 17 October 2014.

**Electronic supplementary material:**

The online version of this article (doi:10.1186/s13063-016-1584-x) contains supplementary material, which is available to authorized users.

## Background

The incidence and the prevalence of chronic diseases have increased steadily in recent decades and are continuously rising. Ageing is an important current issue – patients with chronic diseases, such as chronic heart failure (CHF), chronic obstructive pulmonary disease (COPD), hypertension, and diabetes, are increasing in number and living longer [1, 2]. Till now, health care has been dominated by single-disease approaches lacking coordination and integration [3]. Although, in real life, diseases often coexist in the same patient, the approach to coexistent diseases has been largely neglected. In particular, COPD and CHF frequently coexist due to common risk factors, causing a significant deterioration in these patients’ quality of life (QoL) and increasing morbidity and mortality [2, 4]. The prevalence of COPD in CHF patients ranges from 20 to 32 %, while CHF is prevalent in more than 20 % of patients with COPD [2, 4, 5]. Patients with combined COPD and CHF are often frail and are characterized by a high risk of frequent exacerbations and often the need for rehospitalization, with the related burden of cost [2]. Each disease is an independent predictor of morbidity, mortality, impaired functional status, and health service use [6, 7]. The combination of these two diseases presents many diagnostic challenges [5]. Clinical symptoms and signs require careful interpretation, in conjunction with objective evidence for each condition. Both are chronic progressive diseases with a course that fluctuates, burdened by frequent exacerbations, through a vicious circle of dyspnea, decreased activity, new exacerbations [8, 9], depression, and social isolation, ultimately leading to death [10, 11]. Muscle mass loss and skeletal muscle wasting in these patients have serious therapeutic and clinical implications [12]. Muscle atrophy contributes to muscle fatigue during exercise, obliging patients to stop exercising even if they have not yet exhausted their heart and lung capacity [12, 13].

The weight of evidence from randomized trials in these single specific diseases indicates that a multidisciplinary disease-management approach, supported by telecommunication technologies, has the best outcome in terms of prolonged survival and reduced hospital readmission rates [14, 15]. However, in patients where these two chronic diseases coexist there is no similar evidence to date.

We previously presented, in CHF [16] and COPD patients [17], a model for a multidisciplinary care approach using structured telephone support providing medical/nursing interventions coupled with biosignal telemonitoring. This model demonstrated a possible approach for chronic single-disease treatment after hospitalization, providing a way to prevent clinical deterioration and rehospitalizations through a comprehensive, long-term intervention with regular reinforcement of patient adherence, knowledge, and skills [18]. No physical rehabilitation program was included in this model.

## Methods/design

### Aims

A personalized hospital discharge program appears to be the best approach for the follow-up care of patients with combined COPD/CHF. Particularly important for patients with multiple comorbidities is routine self-management support, consisting of education to help patients to recognize symptoms early, manage their medical devices, identify barriers to adherence to therapy such as adverse effects of drugs, and check that the intensity of physical therapy is appropriate. Our study aims to compare the feasibility and efficacy of an integrated, home-based, medical/nursing intervention plus a physical rehabilitation program versus conventional care in patients with combined COPD/CHF. The purpose of this paper is to describe the rationale and design of the trial.

### Design

This is a consecutive, multicenter, open, randomized controlled trial. All enrolled patients have been followed for 4 months at home and visited at hospital discharge (T0), after 4 months (T1) and again after another 2 months (T2), on which occasion the same tests performed at the two previous visits were repeated. A flow chart of the study design. is shown in Fig. 1.

**Fig. 1 Fig1:**
[figure not shown]
Study flow chart

The study strategy is registered, constructed and presented according to the recommendations for Interventional Trials (SPIRIT) [19] (SPIRIT checklist, Additional file 1) and Consolidated Standards of Reporting Trials (CONSORT) guidelines [20].

### Study sites and patient population

Patients were recruited consecutively from the Cardiology and Pulmonary Departments of three rehabilitation hospitals in Italy (Salvatore Maugeri Foundation IRCCS Institutes of Lumezzane and Montescano; and San Raffaele Pisana IRCCS, Rome). Patient selection criteria are listed in Table 1. CHF and COPD diagnoses had to be documented from at least one echocardiogram (CHF) performed within the previous 12 months under clinically stable conditions [21] and by a spirometry examination (COPD) [6] performed within the previous 12 months.

**Table 1 Tab1:** Eligibility criteria

Inclusion criteria	Exclusion criteria
1. Age over 18 years	Physical activity limitations due to noncardiac and/or pulmonary conditions
2. Chronic obstructive pulmonary disease (COPD) GOLD classification (classes B, C, and D) [11]	Limited life expectancy
3. Systolic and/or diastolic heart failure (HF) New York Heart Association (NYHA) classes II, II, and IV	Severe cognitive impairments
4. At least one hospitalization or visit due to HF or COPD exacerbation in the previous 12 months	
5. Signed informed consent	

### Randomization

Consenting eligible patients were randomized to either an intervention or a control group (1:1). A computer generated tables to allocate patients in fixed blocks of 4. In order to prevent selection bias, the allocation sequence was concealed from the investigators enrolling and assessing patients, in sequentially numbered, opaque, sealed envelopes.

Due to the nature of the intervention, neither the patients nor the physicians were blinded to patients’ group allocation; however, outcome assessors and data analysts will be blinded.

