### Trial structure

The trial structure of the study is described in the Table 2. A specially trained nurse-tutor (NT) and physiotherapist (PT) screened the electronic patient boards every week at each rehabilitation hospital for eligible candidates for the study and checked their eligibility in terms of the inclusion and exclusion criteria with the study doctor. If any possible candidates had been admitted in the previous week the patients were informed verbally and in writing about the study by the study team. Before discharge from hospital to home (T0), all candidates underwent assessment of arterial blood gases and nutritional status by Body Mass Index (BMI). Then patients were also administered the following evaluations or scales:

**Table 2 Tab2:** Trial structure of the study

Activity/Assessment	Pre visit	T0	T1	T2
	During hospitalization	Visit 1	Visit 2	Visit 3
		Baseline (before discharge)	After 4 months	After 2 further months
Prescreening consent	X			
Consent Form		X		
Inclusion/Exclusion Form	X			
Arterial blood gases		X	X	
Body Mass Index (BMI)		X	X	
6MWT		X	X	X
MRC scale		X	X	X
Borg scale		X	X	X
Barthel Index		X	X	X
PASE		X	X	X
MLHFQ		X	X	X
CAT		X	X	X
Triage to assess the patient’s compliance to the rehabilitation program (only in the intervention group)			X	
Customer satisfaction (only in the intervention group)			X	

Evaluation of exercise capacity by the 6-min Walk Test (6MWT) [22]Assessment of dyspnea in activities of daily living (ADL) by the Medical Research Council (MRC) scale [23]Assessment of dyspnea and muscle fatigue in ADLs by the Borg scale [24] – patients were asked to report their own sensations referring to the previous dayEvaluation of disability by the Barthel Index [25]Indirect assessment of physical activity by the Physical Activity Scale for the Elderly (PASE) [26]Assessment of QoL by the Minnesota Living with Heart Failure Questionnaire (MLHFQ) [27] and by the COPD Assessment Test (CAT) [28]

Then, patients were randomized into one of the two groups. The same measurements were repeated after 4 months (T1) and after a further 2 months of follow-up (T2).

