## Discussion

With the progressive ageing of the general population, there is a need to develop more intensive and integrated rehabilitation interventions for the growing number of more complicated, disabled, high-risk patients. The aim of our study was to provide patients with combined COPD/CHF (complex and frequently frail patients with a very high risk of rehospitalization) with an integrated, multidisciplinary NT- and PT-oriented program at the time of in-hospital rehabilitation discharge. This would be characterized by improved knowledge of the signs and symptoms of their disease, with interventions on self-management in the use of medications, evaluation and solution of problems related to exacerbations according to a personalized action plan (self-management), continuous education at a distance with the possible use of a specialist network for a second opinion via remote surveillance (self-guided), home visits as needed, and a guided rehabilitation maintenance program (home care).

Despite the increasing incidence of chronic diseases and, among them, the high prevalence of CHF and COPD, there are no studies in the literature dealing with a similar home-care approach supported by telemedicine in this patient population, where the coexistence of both diseases implies a far greater functional deficit and impact on QoL than in other chronic conditions. Through this program, the NT and PT, with the support of the physician, actively monitored the clinical situation and the patient’s physical status, modifying the therapeutic approach and the workload weekly.

To minimize bias we used consecutive enrollment and central randomization. Due to the nature of the trial it was not possible to blind patients and health care personnel. We tried to standardize as much as possible the nursing and physiotherapy approach in the three hospitals involved in patient enrollment, conducting joint training of staff, organizational meetings and planning before commencing patient enrollment. The rehabilitation program adopted at home tried to reproduce as much as possible the rehabilitation carried out in the hospital, at the same time personalizing the program to the needs of patients.

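### The Discussion claims central randomization, but only sealed envelopes in fixed blocks of 4 are described; up to a third of allocations could be deduced if lists ran per hospital and the block size was known

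*Protocol article*

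**What the plan says.** The Randomization section of the Protocol article gives 1:1 allocation and the mechanism: "A computer generated tables to allocate patients in fixed blocks of 4", with the sequence held "in sequentially numbered, opaque, sealed envelopes". It states that "the allocation sequence was concealed from the investigators enrolling and assessing patients". On blinding it says that "neither the patients nor the physicians were blinded", while "outcome assessors and data analysts will be blinded".

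The Discussion names a different safeguard: "To minimize bias we used consecutive enrollment and central randomization".

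On recruitment, the Trial structure section says that "A specially trained nurse-tutor (NT) and physiotherapist (PT) screened the electronic patient boards every week at each rehabilitation hospital" and that these staff checked eligibility with the study doctor. Randomization followed consent and the T0 tests. Under Interventions, the same two roles educate and follow the patients in the intervention arm.

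The Statistical analysis section gives one model for the training effect, a repeated-measures ANOVA with time and group as factors. Centre is not named. The article does not say whether there was one list or one per hospital, who held the envelopes, or whether staff were told the block size.

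**The concern.** Sealed envelopes hide the next assignment only if it cannot be worked out from the previous ones. A small block of constant size, in a trial where assignments become known, weakens that protection. Staff who both screen and treat learn who entered the program and, by elimination, who did not. Someone who knows the next arm could hasten, delay or discourage a frail candidate. Several exclusion criteria, such as limited life expectancy, have no threshold in Table 1 and leave room for judgement. Blinded outcome assessment protects the measurement of the 6-min Walk Test (6MWT); it does not protect the make-up of the arms.

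True central allocation, with assignments released one at a time across three hospitals, would largely remove the problem. It therefore matters that the Discussion claims it and the Randomization section does not describe it. A reader judging risk of bias would reach different conclusions from the two sections.

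A second, smaller matter is that care was delivered by hospital-based teams. If change in 6MWT differs between hospitals, a model with time and group only leaves that variation in the error term. If the blocks ran within hospital, the model also ignores the structure of the randomization.

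**Working it through.** **The plan's own figure.** Sample size section: difference 30 m, SD 50 m, 80% power, 5% level (two-sided assumed). n = 2 × (1.96 + 0.842)² × 50² / 30² = 43.6, so 44 per group. Dropout of 20–25% gives 44/0.80 = 55 and 44/0.75 = 58.7, so 59. Both agree with the article, and neither depends on this point. Planned enrolment is 110–120 in total.

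**Case A: one list per hospital, block size known, all earlier assignments on the list seen.** A 1:1 block of 4 has six equally likely orderings, hence 24 positions.
- Position 4 is always determined: 6 positions.
- Position 3 is determined when the first two are alike, in 2 of 6 orderings: 2 positions.
- Certain allocations: 8/24 = 33.3%, or 37 of 110 to 40 of 120.
- Success when guessing the arm with more places left, by position: 1/2, 2/3, 2/3, 1. The mean is (0.500 + 0.667 + 0.667 + 1)/4 = 17/24 = 70.8%, against 50% with no information.

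**Case B: one list shared by three hospitals of equal size (assumed), each seeing only its own assignments.** Certainty now requires that both earlier patients of the exhausted arm came from the observer's hospital, which has probability (1/3)² = 1/9.
- Position 3: 1/3 × 1/9 = 1/27.
- Position 4: 1/9.
- Average over four positions: (0 + 0 + 1/27 + 1/9)/4 = 1/27 = 3.7%. Simulation gave the same 3.7%, with guessing success of about 57%.

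**What the constant block size contributes.** With blocks of 4 and 6 mixed at random and about 40 patients per list, simulation gives about 6% certain allocations and 69% guessing success. Varying the size removes most of the certainty but little of the guessing advantage.

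**Centre in the model.** Take change scores with within-centre SD 50 m, 44 per group, and allocation balanced within three centres. The signal is 30 / (50 × √(2/44)) = 2.81 standard errors.
- No centre differences: power is Φ(2.81 − 1.96), about 80%. By simulation it is 79.9% without centre and 79.7% with it.
- Centre SD of 30 m in change (an assumed value): the unadjusted residual variance averages 2500 + 900 × 2/3 = 3100, an SD of 55.7 m. The critical value rises to 1.96 × 55.7/50 = 2.18 true standard errors, so power is Φ(2.81 − 2.18), about 74%. By simulation it is 73% without centre and 79% with it.

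These gains arise only if centre acts on change. A centre main effect alone leaves the time-by-group test as it was.

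**The case against.** The two statements are not strictly incompatible. A list can be generated, or envelopes held, at one place and still be dispensed in envelopes. Taken at face value, central randomization points towards a single list, where the one-third figure does not apply. The article also states concealment from the investigators who enrolled and assessed patients, consecutive recruitment, weekly board screening, and an eligibility check with the study doctor. All of this stands. It means that a third is an upper bound, and that the Discussion cannot be called false, only unsupported by the mechanism described. It does not remove the need to reconcile two sections on a core safeguard.

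A reader might infer that a third of allocations were in fact predictable, or that arms were steered. The documents support neither. They do not mention lists by hospital or disclosure of block size, they do not say that the same individuals screened and treated (only the same roles), and nothing suggests that enrolment was manipulated. Even if arms differed at T0, the effect is planned as change from T0, so a difference in level would not carry over one for one.

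On centre, no stratification is stated, so a time-and-group model contradicts nothing, and a separate analysis plan may add centre. Joint staff training may also have reduced differences between hospitals. That leaves centre adjustment as a cheap improvement to the model as stated; its omission is not an error.

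**Conclusion.** The point holds as a conditional one. The Discussion rests its protection against bias on central randomization; the Randomization section describes envelopes in fixed blocks of 4, in an open trial whose screening roles also treat. Between about 4% and 33% of allocations could have been deduced with certainty. The upper end assumes one list per hospital, a known or inferred block size, and sight of all earlier assignments on that list. The lower end assumes a shared list, equal recruitment, and sight of local assignments only. The article does not say where in this range the trial lies, and no selection bias is shown.

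Adding centre costs almost nothing if hospitals do not differ (79.9% against 79.7% power). It recovers about six percentage points (73% to 79%) if change varies between hospitals with an SD of 30 m, a value assumed here because the article gives none.

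**What to change.** 1. Reconcile the Randomization section and the Discussion by stating what was done: one list or one per hospital, who held and opened the envelopes, and whether the block size was disclosed to recruiting staff. If allocation was not central, drop or qualify that claim. Report the fixed block size as a limitation. Enrolment ended in October 2014, so the block size cannot be changed. Cost: a few sentences.

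2. Before the analysts are unblinded, add centre to the stated model so that it acts on change. Use either centre and centre-by-time in the repeated-measures model, or centre in an analysis of T1 adjusted for T0. Cost: about two degrees of freedom. The benefit is precision, and correct standard errors if lists ran per centre. If unblinding has already happened, present the adjusted analysis as a labelled addition.

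3. Optional: check T0 6MWT against the allocation probability implied by earlier assignments in the block (the Berger-Exner approach). This is possible only once the list structure is known. With 110–120 patients its power is limited, so a null result would not be strong reassurance.

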### Trial structure

The trial structure of the study is described in the Table 2. A specially trained nurse-tutor (NT) and physiotherapist (PT) screened the electronic patient boards every week at each rehabilitation hospital for eligible candidates for the study and checked their eligibility in terms of the inclusion and exclusion criteria with the study doctor. If any possible candidates had been admitted in the previous week the patients were informed verbally and in writing about the study by the study team. Before discharge from hospital to home (T0), all candidates underwent assessment of arterial blood gases and nutritional status by Body Mass Index (BMI). Then patients were also administered the following evaluations or scales:

**Table 2 Tab2:** Trial structure of the study

Activity/Assessment	Pre visit	T0	T1	T2
	During hospitalization	Visit 1	Visit 2	Visit 3
		Baseline (before discharge)	After 4 months	After 2 further months
Prescreening consent	X			
Consent Form		X		
Inclusion/Exclusion Form	X			
Arterial blood gases		X	X	
Body Mass Index (BMI)		X	X	
6MWT		X	X	X
MRC scale		X	X	X
Borg scale		X	X	X
Barthel Index		X	X	X
PASE		X	X	X
MLHFQ		X	X	X
CAT		X	X	X
Triage to assess the patient’s compliance to the rehabilitation program (only in the intervention group)			X	
Customer satisfaction (only in the intervention group)			X	

Evaluation of exercise capacity by the 6-min Walk Test (6MWT) [22]Assessment of dyspnea in activities of daily living (ADL) by the Medical Research Council (MRC) scale [23]Assessment of dyspnea and muscle fatigue in ADLs by the Borg scale [24] – patients were asked to report their own sensations referring to the previous dayEvaluation of disability by the Barthel Index [25]Indirect assessment of physical activity by the Physical Activity Scale for the Elderly (PASE) [26]Assessment of QoL by the Minnesota Living with Heart Failure Questionnaire (MLHFQ) [27] and by the COPD Assessment Test (CAT) [28]

Then, patients were randomized into one of the two groups. The same measurements were repeated after 4 months (T1) and after a further 2 months of follow-up (T2).

Only in the patients of the intervention group, we evaluated:The percentage of the prescribed training sessions that were actually performed (number of performed sessions as a percentage of the total scheduled training sessions); in addition, the PT filled out a 5-point Likert scale (see Table 3) at the T1 visit, assessing the collaboration and compliance of patients in the intervention group

**Table 3 Tab3:** Triage to assess a patient’s compliance to the rehabilitation program

0	*Nothing*: the patient has never followed the changes to the program of retraining provided by the physiotherapist
1	*Little*: the patient has followed for less than half of the time the information provided by the physiotherapist
2	*Medium*: the patient has followed for about half of the time the information provided by the physiotherapist
3	*Sufficient*: the patient has followed for more than half of the time the information provided by the physiotherapist
4	*Very much*: the patient has always followed the changes to the program of retraining provided by the physiotherapistSatisfaction regarding the assistance was measured by the patient at T1. The six items, with a score from 0 (not at all satisfied) to 4 (very satisfied), enquired about the service as a whole, the use of the devices, the health care professionals’ willingness to respond to the patient’s needs, clarity of the indications and suggestions made by the NT and PT, the feeling of support, and if the service was felt to be of real help or not (Table 4)

**Table 4 Tab4:** Customer satisfaction

1. How do you judge the system overall?	
a. Not satisfying at all	0
b. Poorly satisfying	1
c. Fairly satisfying	2
d. Quite satisfying	3
e. Very satisfying	4
2. Was it easy to use the devices?	
a. Very complicated	0
b. Quite complicated	1
c. Complicated	2
d. Quite easy	3
e. Very easy	4
3. Did you experience difficulties in contacting the service?	
a. Very frequently	0
b. Frequently	1
c. Sometimes	2
d. Rarely	3
e. Never	4
4. Were the indications of the health staff clear?	
a. Not at all	0
b. Poorly clear	1
c. Fairly clear	2
d. Quite clear	3
e. Very clear	4
5. Do you feel more secure since when you have access to the service?	
a. Not at all	0
b. Poorly	1
c. Fairly	2
d. Much	3
e. Very much	4
6. Did the access to the service help your family or the people you live with?	
a. Not at all	0
b. Poorly	1
c. Fairly	2
d. Much	3
e. Very much	4

